## Methods

### Overview

This study protocol was developed in accordance with the recommendations for interventional trials 2013 statement SPIRIT (Standard Protocol Items: Recommendations for Intervention Trials) [27] and SPIRIT-AI (SPIRIT–Artificial Intelligence) guidance published for trials of AI interventions [28].

### Study Design and Setting

A randomized, controlled, double blind, parallel, multicenter trial was conducted in 2 populations (general population and individuals with T1D) in 3 European countries. For this purpose, participants were provided either with the WARIFA app with personalized recommendations or the same WARIFA app without personalized recommendations. The participating centers are: the Research Institute for Biomedical and Health Sciences, University of Las Palmas de Gran Canaria, Gran Canaria, Spain, associated with Complejo Hospitalario Universitario Insular Materno-Infantil; and the National Center for eHealth, Tromsø, Norway. In Romania, it is led by Netsun.

### Participants and Recruitment

Participant eligibility criteria for recruitment are presented in Textbox 1.

Inclusion and exclusion criteria.
**Inclusion criteria**
Common to both populations: adults aged 18 years and older with an Android smartphone and internet access.General population group: healthy or diagnosed with no more than one noncommunicable disease (NCD; cardiovascular disease [CVD], cancer, type 2 diabetes [T2D], or chronic obstructive pulmonary disease [COPD]).Type 1 diabetes (T1D) group: diagnosed with T1D, treated with multiple insulin injections, and using a continuous glucose monitor of the brand Freestyle Libre (FSL; Abbott).
**Exclusion criteria**
Common to both groups: individuals aged 18 years and younger, pregnancy, mobile phone incompatible with the WARIFA (Watching the Risk Factors) app (eg, Apple devices), not understanding any of the languages used in the app (English, Spanish, Norwegian, and Romanian), or any other reason that precludes follow-up.General population: people with 2 or more NCDs (CVD, cancer, T2D, or COPD).

### Randomization and Blinding

After registration in the WARIFA app, participants were randomly assigned in a 1:1 ratio by the system, using a computer-generated randomization list. This randomization was stratified by T1D status (yes or no) and center, to ensure balance within each group. The app was downloaded from Google Play, with the same download link for all participants, who were unaware of what exactly to expect from the app. Once downloaded, and after registration, eligibility criteria were confirmed, informed consent was given within the app and participants were randomized: one feature set in the app was available for the control group and another for the intervention group. This procedure was done individually by the participants, avoiding interaction amongst them. Both the researchers and the participants were unaware of group allocation, and the researchers who analyze the data are blinded, too.

In the Norwegian and Romanian centers, the app was downloaded either independently by the participant or with assistance (Norway). In the Spanish center, visits were face-to-face, as blood tests and physical examinations were carried out.

### Intervention

The intervention consists of 12 weeks using a version of the WARIFA app with personalized risk estimations for different NCDs and individualized recommendations, based on each participant’s personal preferences.

To do this, the app uses a simple and intuitive interface, using data available from public databases (for UV index and air quality index) and data from the participants themselves (entered manually, via questionnaires, or automatically, via sensors). The app uses AI to create rule-based recommendations and feedback based on scientific evidence and behavior change models. Bayesian belief networks are used to assess individual risk for CVD in participants with T1D [29], and deep learning for the prediction of glucose values based on previous CGM data [30].

The WARIFA app is downloaded to participants’ own smartphones, who are also provided with a physical activity monitor (Samsung Galaxy Fit 3) to track physical activity, heart rate, and sleep. This is connected to the WARIFA app. Participants with T1D use their glucose sensors (Free Style Libre [FSL] 2 and 3, Abbott), also linked to the WARIFA app.

Participants aimed to use the app for 12 weeks, with 2 face-to-face visits (in Spain only): one at the start of the study and one at the end of the study. At the first visit, the app was downloaded and linked to the activity monitor (all participants) and glucose monitors (T1D participants only). Both visits included blood tests and a physical examination. The Norwegian and Romanian centers did not perform in-person studies, and all participant information was provided through the app in these countries. Questionnaires were completed within the app itself in all centers.

The WARIFA app includes several functionalities (Figure 1):

My day: a diary is available to record various items [Figure 1H]. Participants are able to easily and intuitively record their fruit and vegetable intake, alcohol and tobacco consumption, and sunscreen use every day. They are able to customize the diary to choose the items they want to record. They see a graphical presentation of the records of the last 7 days, with a marker for their personal goal [Figure 1I], as well as individual and personalized messages generated with the use of AI for the improvement of their goals. People with T1D can also record their hypoglycemic events.Assess your lifestyle: participants complete questionnaires that provide data for WARIFA to personalize their risk estimation and recommendations. These questionnaires include basic variables (age, gender, weight, and height), lifestyle habits (alcohol consumption, smoking, and physical activity), eating habits, and sun exposure, as well as additional risk factors for melanoma. Once the questionnaires have been completed, the app delivers the first messages with personalized recommendations. If the user enters this section at another stage in the trial and changes data in the questionnaires, new recommendations are generated and delivered to the user.My top recommendations: personalized recommendations appear for each participant each day, based on the data obtained through the initial questionnaires and how far they are from the recommended target for each item (Figure 1A). These recommendations are based on scientific evidence and updated World Health Organization guidelines.My health predictions: will give access to risk calculators (Figure 1B) for different NCDs (T2D, CVD, COPD, and melanoma) with personalized risk estimation over the next 10 years. During the WARIFA project, some risk calculators were developed, including the cardiovascular risk calculator for T1D [29]. The melanoma risk calculator was developed based on the first primary risk prediction tool created by the Melanoma Institute Australia [31]. The FINDRISK calculator, which has been validated in several European countries, is used to calculate the risk of T2D [32]. To calculate cardiovascular risk in the general population, the SCORE2/SCORE2OP calculator was used; this has been validated in the European countries participating in the study [33,34]. Finally, the self-scored COPD population screener questionnaire [35] was used to screen for COPD in smokers, since there is no COPD risk calculator validated in the European population. In all cases, the personalized risk of the different NCDs is accompanied by an explanatory message. If the COPD-Q score is high, it is recommended that participants visit their health service physician for further assessment.My community: through the use of geolocation (if permission is granted), it provides personalized recommendations based on the UV and air quality indices in the participant’s geographical area (Figures 1C,1D,1E,1F, and 1G). A link to a web page [36] with additional health-relevant information (air pollution and UV rays, statistics on NCDs of the population, lifestyle habits...) about the area where the user is located is also displayed.Step functionality: shows the number of steps taken by participants at any point in each day, as well as a graphical presentation of the number of steps for the last 7 days (Figure 1J). Recording is automatic via the physical activity monitor.Heart rate function: shows the current heart rate and a graph with its evolution in relation to the measurements in the last 24 hours. The source of the data is the physical activity monitor.Sleep function: shows today’s hours of sleep and a bar graph of the hours of sleep the last 7 days recorded by the physical activity monitor.Diabetes functionality: people with T1D can view their glucose data in near real time (with a delay of 30 minutes) by connecting to the glucose sensor (Figure 2). They can also view historical glucose data through various graphs, such as time in different ranges (Figures 2B and 2C), glucose management index, and hypoglycemic events. Using AI, they receive an estimate of the interstitial glucose prediction over the coming 30 minutes and 2 hours (Figure 2D), as well as a personalized risk of nocturnal hypoglycemia (Figure 2A).Settings and other functions: in this section, participants can customize which parts of the WARIFA app they want to see, as well as the notifications, sounds, fonts, and language used.

**Figure 1 figure1:**
[figure not shown]
Functions of the WARIFA app: (A) Personalized recommendations; (B) Risk calculators for different noncommunicable diseases and chronic obstructive pulmonary disease screening; (C) My community functionality, including the UV index (D) and recommendations (E); and (F) air quality with recommendations (G). (H) Diary functionality and viewing statistics for the last 7 days (I). (J) Steps functionality and comparison with the previous seven days. (K) The main. (L) Options menu.

**Figure 2 figure2:**
[figure not shown]
Diabetes features: (A) Overnight hypoglycaemia prediction functionality; (B) display of % range times in the last month; (C) comparison of monthly range times; and (D) glucose prediction functionality.

### Control Group

The control group received a low-intensity intervention, with access to a WARIFA app version where almost all the functionalities mentioned above are available, except for the diary, risk calculators, and personalized recommendations. AI features such as near real-time glucose prediction, night time hypoglycemia risk, and motivational feedback in the top recommendations section are not available in this version, either. Data are collected in a similar manner, and an activity monitor is provided for the duration of the study, too.

### Patient and Public Involvement

Potential end-users, including a T1D patient association, were involved during the co-creation of the WARIFA app. The results of the RCT will be presented in an open access research article, as well as on the project website and on the European Commission’s CORDIS platform [37].

### Outcomes

#### Overview

The primary outcome is a participant-defined goal, whose fulfillment is assessed at the end of the study using a Likert scale ranging from 1 (“far below expectations”) to 10 (“far above expectations”) [38].

Participants can choose their own goal from a range of options: increase fruit and vegetable consumption, increase physical activity, reduce alcohol consumption, stop smoking, improve sun protection behavior, and reduce the number of weekly hypoglycemic episodes (the latter only for T1D participants).

The secondary outcomes are: frequency of app use, time spent using the app, consistency in data recording, changes in eating habits, increase in physical activity, reduction in smoking and alcohol consumption, changes in sun protection behavior, total cholesterol, high-density lipoprotein (HDL) cholesterol, low-density lipoprotein cholesterol, non-HDL cholesterol, triglycerides, weight, BMI, body fat, lean mass, abdominal, waist and biceps circumference, abdominal skinfold thickness, tricipital skinfold thickness, dynamometry, sit to stand 5 repetitions test, perceived quality of life, acquired knowledge, self-efficacy, and usability.

For participants with T1D, hypoglycemic events (number of episodes of at least 15-minute duration with a glucose concentration of <70 mg/dL according to the CGM and manually registered episodes), HbA_1c_, average glucose (average glucose in mg/dL over the last 14 days), glucose management indicator (a measure of glycemic control calculated from average glucose, which is an estimation of HbA_1c_) and time in target range (% of time in the last 14 days that glucose is within (70-180mg/dL), below (<70 mg/dL), above (181-240 mg/dL), or significantly above (>240 mg/dL) the recommended target will be measured.

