#### Direct Adherence

Adherence is measured by frequency of app use (number of times participants log in per day), duration of use (number of hours per day), and consistency of data recording (interactions with the app, like using the diary, changes in the questionnaire answers, and entering hypoglycemia data).

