#### Biomedical Outcomes

A blood test and physical examination were only carried out in Spain. A blood test was performed at the beginning and end of the study to measure blood count, creatinine, urea, glucose, glutamic pyruvic transaminase, glutamic oxaloacetic transaminase, gamma-glutamyl transferase, total cholesterol, HDL cholesterol, and triglycerides in all participants. Automated, routine colorimetric methods are used. Non-HDL cholesterol is calculated by subtracting HDL from total cholesterol, and low-density lipoprotein cholesterol is estimated using Friedewald’s formula [39]. HbA_1c_ was measured by High-Performance Liquid Chromatography (using Diabetes Control and Complications Trial standards, following National Glycohaemoglobin Standardisation Programme) in people with T1D only.

As part of the physical examination, the patient’s weight and height were measured to calculate BMI. Measurements of the abdomen, arm, and calf circumference are taken with a non-extensible measuring tape. Grip strength is assessed using a Jamar dynamometer, and a Holtain plicometer (Holtain Ltd) is used to measure the triceps skinfold. Body fat and muscle mass are estimated using a Tanita DC-360 (Tanita) bioimpedance meter. Arm muscle circumference is calculated from the triceps skinfold and arm circumference measurement. Muscle quality is calculated based on the muscle mass from the bioimpedance analysis and the grip strength measurement [40]. Finally, the functional test sit-to-stand with 5 repetitions is performed [41].

For participants with T1D, time in relevant ranges (see above), average glucose, glucose management indicator, and hypoglycemic events are recorded by the app from a CGM FSL 2 or 3 (Abbott). Hypoglycemic events are also recorded or confirmed manually.

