### Power and Sample Size

The sample size was calculated for the primary outcome (Likert scale from 1 to 10 with a target defined by the participant). A population of people with T1D was used as the reference population, based on a previous study [38,49]. The common SD in the intervention and control groups is assumed to be 2.07 [38]. With a significance level of 0.05 and a power of 0.8 in a 2-sided 2-sample *t* test (2-tailed), 47 subjects are necessary in both groups to detect a statistically significant difference greater than or equal to 1.3 units. Allowing for a potential loss to follow-up of 10%, we estimated a total required sample size of 52 participants in each group. Participants with T1D are only recruited in Spain. All 3 centers aimed to recruit an equal number of participants, that is, 36 participants each (aiming at a total of 108).

The analyses will primarily be performed on the total sample for common outcomes. Regarding the group of participants with T1D, as the study lacks the power to detect clinically relevant changes in T1D-specific clinical outcomes, no definitive conclusions will be drawn from these results. Instead, the results will inform sample size estimation and the design of a subsequent trial targeting the T1D population specifically.

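### Hypoglycemic events include manual entries, but the only manual route described is in a diary the control app lacks, so ascertainment can differ by arm

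*Protocol article*

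**What the plan says.** All references are to the protocol article, Methods.

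- **Outcomes, Overview** defines the T1D event outcome with two sources: "number of episodes of at least 15-minute duration with a glucose concentration of <70 mg/dL according to the CGM and manually registered episodes".
- **Intervention** introduces the functionality that holds manual entry as "My day: a diary is available to record various items". Within that same item it adds: "People with T1D can also record their hypoglycemic events". The separate Diabetes functionality item covers viewing glucose data and past events and receiving predictions. It mentions no manual entry.
- **Control Group** gives the control app nearly all functions "except for the diary, risk calculators, and personalized recommendations". It then says: "Data are collected in a similar manner, and an activity monitor is provided for the duration of the study, too".
- **Direct Adherence** gives examples of interactions with the app: "like using the diary, changes in the questionnaire answers, and entering hypoglycemia data".
- **Biomedical Outcomes** says the app records events from the CGM for participants with T1D, and adds: "Hypoglycemic events are also recorded or confirmed manually". Neither statement is restricted to one arm.
- **Objective and Hypothesis** expects the app to lower the number of hypoglycemic events.
- **Power and Sample Size** says the T1D-specific clinical outcomes are underpowered and will not support firm conclusions, but that "the results will inform sample size estimation and the design of a subsequent trial targeting the T1D population specifically".

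**The concern.** A between-arm comparison of event counts needs events to be captured in the same way in both arms. Sensor capture appears to be the same: nothing in the article limits CGM recording to one arm. Manual capture does not appear to be the same, because the only place described for it is a feature withheld from control participants. Randomisation does not correct a difference in how the outcome is ascertained.

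If manual entries contribute events beyond those the sensor holds, the extra events can arise only where manual entry is possible. The comparison would then be pushed against the effect the trial expects, and a real reduction could look smaller or absent. The T1D results are meant to feed the planning of a later trial, so an event rate or effect estimate affected in this way could be carried into it if this outcome is the one used.

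**Working it through.** The article states no figure for manual entries, so there is none to reproduce. The check sets the sections side by side and then illustrates the direction.

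**Step 1: is manual entry part of the outcome?** Yes. The definition under Outcomes, Overview names manually registered episodes beside CGM episodes.

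**Step 2: where is manual entry described?** Under Intervention, inside the My day item, which is the diary. The Diabetes functionality item offers no second route.

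**Step 3: does the control app have the diary?** No. Control Group lists it first among the features removed.

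**Step 4: is another control route described?** None is. Three sentences nevertheless leave the possibility open:

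| Section | What it suggests | What it does not say |
|---|---|---|
| Control Group | Data collection is similar in both arms | Which data, or by what route hypoglycemia is entered without a diary |
| Direct Adherence | Entering hypoglycemia data is listed beside diary use, as if distinct | Where else it is entered, or in which arm |
| Biomedical Outcomes | Manual recording applies to participants with T1D generally | How control participants would do it |

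The sections therefore do not agree on whether control participants can register an event by hand.

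**Step 5: direction and possible size if the route is diary-only and manual-only entries are added.** Let m be the number of manual-only entries in the intervention arm as a share of its CGM-detected episodes, with m = 0 in the control arm. Then

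observed rate ratio = true rate ratio × (1 + m),

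and a true proportional reduction of m / (1 + m) is fully masked. Both m and the true ratio of 0.80 are assumptions; the article gives neither.

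| Assumed m | No true effect: 1 + m | True ratio 0.80: 0.80 × (1 + m) | Reduction fully masked: m / (1 + m) |
|---|---|---|---|
| 0 | 1.00 | 0.80 | 0% |
| 0.05 | 1.05 | 0.84 | 4.8% |
| 0.10 | 1.10 | 0.88 | 9.1% |
| 0.20 | 1.20 | 0.96 | 16.7% |
| 0.30 | 1.30 | 1.04 | 23.1% |
| 0.50 | 1.50 | 1.20 | 33.3% |

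Here m counts only entries with no matching CGM episode. An entry that merely confirms a sensor episode, and is counted once, contributes nothing to m.

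**Step 6: effect of the fix.** If the comparison uses CGM-detected episodes only, m = 0 in both arms and the observed ratio equals the true ratio as far as manual entry is concerned.

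**The case against.** The strongest reply has five parts.

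1. **Diary-only entry is an inference.** The sentence on similar data collection, the separate listing under Direct Adherence and the unrestricted wording under Biomedical Outcomes all leave room for a control route that the article does not describe. This stands. A reader might infer that the count is in fact inflated in one arm. The text supports only that it can be.

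2. **The article does not say that the two sources are summed.** The definition could mean a sum, a union with duplicates removed, or two measures reported side by side. This also stands. How entries are combined and de-duplicated, and which count model is used, can properly sit in an analysis plan or full protocol that is not shown. Their absence here is not a fault.

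3. **The direction is conditional.** If manual confirmation were used to discard unconfirmed sensor episodes, a route open only to the intervention arm would lower that arm's count. The article describes no such rule but does not exclude it. Bias against the hypothesis therefore holds for added entries, not for every reading.

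4. **The magnitudes are assumed.** Correct. The table shows how the mechanism works and is not evidence of its size. In particular, the rows where a true benefit appears as harm should not be read as a prediction.

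5. **The consequence is small.** The outcome is secondary, and participants with T1D come only from Spain, where 34 people were recruited in all. The article disclaims firm conclusions for this group. It also plans measures that manual entry cannot affect, such as time below 70 mg/dL, average glucose and HbA1c. This stands and limits the weight of the point. Nor does the article say that the later trial will be sized on this event count, so carry-over is possible but not stated.

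The objection does not remove the mismatch. If control participants have no route, ascertainment differs by arm. If they have one, the descriptions need correcting. Some action follows either way.

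**Conclusion.** The point holds in a limited form. The outcome definition includes manually registered episodes, the only described place to register them is the diary, and the control app has no diary. As written, ascertainment of hypoglycemic events can differ by arm. If manual-only entries are added to CGM episodes, the intervention count can be inflated against the hypothesised reduction.

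This rests on two things the article does not settle: that no other control route exists, and that manual-only entries add to the count. The size cannot be stated. The comparison affected is a secondary one in an underpowered subgroup. It still merits correction, because the results are intended to inform a later trial and the remedy uses data the article describes for both arms.

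**What to change.** 1. Reconcile the Intervention, Control Group, Direct Adherence and Biomedical Outcomes sections. State whether control participants could enter hypoglycemic events by hand and, if so, where.
2. Define the between-arm comparison on CGM-detected episodes only, keeping the article's own criterion (below 70 mg/dL for at least 15 minutes) and expressing it relative to the CGM time available for each participant.
3. Report manual entries separately and descriptively, by arm if both arms had a route.

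The cost is a change of wording in the outcome definition, with no new data collection. Follow-up ended in June 2025, but the article says the data are still being analysed. The change should therefore be recorded, with its date and reason, before the arms are compared on this outcome. The scientific price is that symptomatic events the sensor missed drop out of the comparison and remain only in the descriptive report.
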